### Power calculation

Sample size calculations were adjusted for clustering of patients within clinics. Prior year visit data from the University of Wisconsin and the University of Utah was used to estimate the number of iCPR triggers during the study period. We assumed 25 clusters or clinics with a control group antibiotic prescribing rate of 30–40% for iCPR eligible encounters and an absolute decrease of 10% in the rate of antibiotic prescribing in the intervention group. The intra-cluster coefficient was estimated to be between 0.01 and 0.05. Sample size calculations were performed with a significance level of 0.05 and 80% power. The estimated sample size for the most conservative assumptions (control group antibiotic prescription rate of 40% and intra-cluster coefficient of 0.05) is 52,457 patient encounters which, based on historical data, should be attained within 2 years.

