### Setting/clinic eligibility

The study is being conducted at primary care clinics associated with the University of Wisconsin and University of Utah medical centers. All General Internal Medicine (GIM) and Family Medicine (FM) primary care clinics at the two institutions were invited to participate. A total of 33 individual clinics (12 GIM clinics, 16 FM clinics, and 5 combined clinics) are participating in the study. Table 1 illustrates the clinic characteristics. Clinics were enrolled by site leads at each medical center. All physicians, nurse practitioners, physician assistants, and residents at participating clinics were eligible to participate. Both sites use the same EHR system (Epic Systems, Verona, WI) and had off-the-shelf capabilities to develop CDS tools in their EHR. Each site was supported by an information technology department that was able to develop and test the components of the iCPR before deployment.

**Table 1 Tab1:** Description of study clinics

	University of Wisconsin	University of Utah
Total no. of clinics	22	11
No. of intervention clinics	12	6
Total no. of providers	268	111
GIM clinics	10	2
FM clinics	12	4
Combined GIM and FM clinics	0	5
No. of providers per clinic	2–29	3–23

*GIM* General Internal Medicine, *FM* Family Medicine

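### The stated 52,457 encounters cannot give 80% power: with 25 clinics, 40% vs 30% and an ICC of 0.05 no number of encounters can, and the 33 enrolled clinics also fall short at that ICC

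*Protocol article*

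**What the plan says.** The protocol article's Power calculation section prints every input. On the number of clusters and the control rate: "We assumed 25 clusters or clinics with a control group antibiotic prescribing rate of 30–40% for iCPR eligible encounters". The effect is "an absolute decrease of 10% in the rate of antibiotic prescribing in the intervention group". On clustering: "Sample size calculations were adjusted for clustering of patients within clinics", and "The intra-cluster coefficient was estimated to be between 0.01 and 0.05". On error rates: "Sample size calculations were performed with a significance level of 0.05 and 80% power"; whether the test is one- or two-sided is not stated. The result for the most conservative combination is given as "control group antibiotic prescription rate of 40% and intra-cluster coefficient of 0.05) is 52,457 patient encounters", which the section expects to reach within 2 years on historical volumes.

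Under Setting/clinic eligibility, the number recruited is larger than assumed: "A total of 33 individual clinics (12 GIM clinics, 16 FM clinics, and 5 combined clinics) are participating in the study". Table 1 lists 12 intervention clinics at Wisconsin and 6 at Utah, so the split is 18 intervention and 15 control. The Randomization section confirms that the clinic is the unit of randomisation.

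**The concern.** When whole clinics are randomised, more encounters per clinic reduce only the within-clinic part of the variance. The between-clinic part is fixed by the number of clinics, so power has a ceiling. For the stated conservative case that ceiling lies well below 80% with 25 clinics, so no required number of encounters exists for the section to report.

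The trial presents 80% power as secured under its least favourable assumptions once an encounter count is reached, and it is not. A reader faced with a null primary result would take it as coming from a trial with 80% power to detect a 10-point reduction. The paragraph also points to the wrong quantity: encounters look like the binding constraint when clinics are.

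**Working it through.** **Inputs.** From Power calculation: alpha 0.05 (taken as two-sided), power 80%, 40% vs 30%, ICC 0.05, 25 clinics (12.5 per arm), 52,457 encounters. From Table 1: 18 vs 15 clinics. Equal cluster sizes are assumed.

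**Step 1: size without clustering.**

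n per arm = [1.96 × √(2 × 0.35 × 0.65) + 0.8416 × √(0.24 + 0.21)]² / 0.10² = 355.9, or 356. The unpooled formula gives 353 and the arcsine formula 355.

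**Step 2: try to reproduce 52,457.** With k clinics per arm and m encounters per clinic, k·m = n × [1 + (m − 1) × ICC], so

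m = n(1 − ICC) / (k − n × ICC).

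This has a solution only if k > n × ICC = 355.9 × 0.05 = 17.8. With k = 12.5 the denominator is −5.3, so no sample size exists and the stated figure cannot be reproduced. At least 36 clinics in total are needed (2 × 17.8 = 35.6).

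**Step 3: check the stated figure directly.** 52,457 / 25 = 2,098 encounters per clinic. Design effect = 1 + 2,097.28 × 0.05 = 105.9. Effective total = 52,457 / 105.9 ≈ 496, against 2 × 356 = 712 needed.

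**Step 4: power for a fixed number of clinics.**

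SE = √{[ICC + (1 − ICC)/m] × [0.21/k₁ + 0.24/k₀]}, where k₁ is the number of intervention clinics and k₀ of control clinics.

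This is 0.0426 for 25 clinics and 0.0374 for 18 vs 15 (1,590 encounters per clinic). Power follows from 0.10/SE, with either a normal or a t reference (clinics − 2 df). At ICC 0.05:

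| Clinics | Encounters | Normal | t |
|---|---|---|---|
| 25 | 52,457 | 65.0% | 61% |
| 25 | unlimited | 65.4% | 62% |
| 33 (18/15) | 5,000 | 72% | 69% |
| 33 (18/15) | 52,457 | 76.2% | 73.5% |
| 33 (18/15) | unlimited | 76.7% | 74.0% |

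The harmonic mean of 18 and 15 is 540/33 = 16.4 clinics per arm, also below 17.8.

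**Step 5: across the stated ICC range** (18 vs 15 clinics, 52,457 encounters, 40% vs 30%):

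| ICC | Normal | t (31 df) |
|---|---|---|
| 0.05 | 76% | 73.5% |
| 0.04 | 85% | 82% |
| 0.03 | 93% | 91% |
| 0.02 | 99% | 98% |
| 0.01 | >99% | >99% |

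The largest ICC that keeps 80% power at 52,457 encounters is about 0.045 (normal) or 0.043 (t) with 33 clinics, and about 0.035 (normal) or 0.032 (t) with 25. The detectable difference at ICC 0.05 with 33 clinics is 10.5 points (normal) or 10.8 points (t).

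**Step 6: other readings of the inputs.**
- *One-sided 0.05, 40% vs 30%:* n = 280, so the floor is 14.0 clinics per arm, still above 12.5. The ceiling with 25 clinics is 76.2%.
- *30% vs 20%, two-sided:* n = 293, so the floor is 14.7 per arm, again above 12.5.
- *25 clinics per arm:* m = 338.1 / 7.2 ≈ 47, a total of about 2,350. That is not 52,457, and 50 clinics conflict with the 33 in the trial.
- *ICC 0.01, 25 clinics:* m = 39.4, a total of about 985.

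**The case against.** The strongest reply accepts the 25-clinic result and disputes how much it matters.

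- **The trial enrolled 33 clinics.** It falls short only at the top of the ICC range, by 4 to 6.5 points. Power is above 80% at an ICC of 0.04 or below. With 30% vs 20% it is about 84% (normal) even at 0.05, and a one-sided test would give about 85%. This stands: the 33-clinic shortfall is modest and confined to the least favourable case. But that is the case for which the protocol claims 80%, and it states no one-sided test.
- **Strata.** Randomisation is stratified by institution and visit volume, and the model has fixed effects for strata. If these removed about 9% of the between-clinic variance (ICC from 0.05 to about 0.0455), 33 clinics would reach 80% with a normal reference; about 15% (to about 0.0425) would do so with t. This is possible, but the Power calculation claims no such gain and the document gives nothing from which to estimate it.
- **Validity.** The planned analysis models clinic and provider effects, the clinics are already randomised, and the second year also serves the maintenance comparison under RE-AIM. All true. The error lies in the stated power, not in the analysis, and the longer follow-up has uses beyond primary-outcome power.

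Where the figure came from is unknown. With 36 clinics, common formulas give about 35,500 to 60,000 encounters, a range that contains 52,457, but that is only a guess at its origin.

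**Conclusion.** The concern holds. For the stated conservative case, 25 clinics cannot reach 80% power at any number of encounters. At 52,457 the power is about 65% (normal) or 61% (t), and a one-sided test does not change the conclusion. With the 33 clinics randomised, two-sided power in that case is 76% (normal) or 73.5% (t), with ceilings of 76.7% and 74.0%. The design has adequate power for a 10-point reduction if the ICC is no higher than about 0.043 (t) or 0.045 (normal).

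These figures assume equal clinic sizes, clustering by clinic only (as in the protocol's own calculation), and no gain from stratum adjustment. The 33-clinic conclusion also assumes a two-sided 0.05 test. The statement is wrong as written and must be corrected.

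**What to change.** Rewrite the Power calculation paragraph:

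1. Withdraw 52,457 as the number of encounters that gives 80% power.
2. Report power for the clinics as randomised (18 vs 15) for 40% vs 30%, two-sided 0.05, with a t reference: about 73% at ICC 0.05, 82% at 0.04, 91% at 0.03 and at least 98% at 0.02 or below. State that these figures assume about 52,457 encounters and no gain from stratum adjustment.
3. Give the detectable difference at ICC 0.05, about 10.8 points.
4. State that the number of clinics limits precision: with 33 clinics at ICC 0.05, going from 5,000 to 52,457 encounters raises power only from 72% to 76% (normal). The encounter count can stay as a forecast of accrual, not as a power target.
5. State the sidedness of the test, and use one reference distribution throughout.

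The cost is one paragraph and a slightly less favourable stated power. No clinics or encounters need to be added, and the randomisation and analysis model are unaffected. As the article describes the trial as ongoing, the correction is best made before results are read.

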### Implementation

We used a staggered roll out of iCPR to evaluate for any problems, ensure appropriate training, and make sure that there was no interference with patient care. iCPR was first deployed at one GIM and one FM clinic. Researchers followed up with the clinic manager and medical director at these clinics within 2 weeks to determine if the rollout should continue. No major problems were identified, and the rollout continued to the remainder of the clinics over the next 12 weeks based on clinic availability for academic detailing. Following implementation in the remainder of the clinics, managers and medical directors were again contacted to determine if any problems had arisen. A contact link was also built into the iCPR alert so that individual providers could contact the researchers with any questions or concerns. The study was launched in October 2015 and is ongoing (Fig. 4).

**Fig. 4 Fig4:**
[figure not shown]
iCPR study flow. *NPT* normalization process theory

### Protocol amendments

Changes to the research protocol that impact conduct of the study will be reviewed by the individual institutional review boards. Ammendments will also be made to the trial registry as necessary.

### Confidentiality

Participants’ anonymity will be maintained. Depersonalized data will be extracted from the EHR and stored on secure servers at each medical center. Transmission of data for analysis will occur via secure file transfer protocol (s-ftp). All documents will be stored securely and accessible only by the trial investigators.

### Dissemination

Trial results will be published in an open access medical journal and posted on ClinicalTrial.gov.

## Discussion

The multi-site iCPR trial builds on the previous single-site study to assess whether CPRs integrated in the EHR can change provider behavior and improve evidence-based care in a broad range of primary care clinics. We focused on the importance of integrating the tool into clinic workflows in order to optimize uptake and clinical usefulness. This required building flexibility into the tool to accommodate a variety of workflows and led to variations in the tool design and workflows between the two health systems. Near-live usability testing evaluated how well we succeeded in workflow integration and reaffirmed the importance of near-live usability testing when implementing new EHR tools. While we designed the tool to be provider-centric, we were forced to make some usability compromises based on limitations in the EHR. The limited points for iCPR triggering and lack of specificity of potential triggers were highlighted in usability testing. However, there were no clear solutions to these issues within the current EHR. EHR systems need to continue to evolve in order to better accommodate the diversity in workflow and clinical decision making. The impact of iCPR on antibiotic prescribing remains to be determined; however, our experience developing this tool for a diverse group of clinics and having clinicians and clinic personnel involved throughout the development process represent a roadmap for delivering evidence-based tools through CDS at the point of care.

## Abbreviations

BPM: Beats per minute
CDS: Clinical decision support
CPR: Clinical prediction rule
EHR: Electronic health record
FM: Family Medicine
GIM: General Internal Medicine
HR: Heart rate
iCPR: Integrated clinical prediction rules
NPT: Normalization Process Theory
URI: Upper respiratory infection
s-ftp: Secure file transfer protocol
